## Abstract

**Introduction:**

Immunosuppression is associated with an increased risk of delayed SARS-CoV-2 viral clearance, severe COVID-19 and related death. This heterogeneous group of affected patients includes but is not limited to those with a haematological malignancy, people on immunosuppressive therapy for the treatment of autoimmune/inflammatory diseases and those following bone marrow transplantation (BMT). Immunosuppression is associated with decreased rates of anti-spike IgG seroconversion following COVID-19 vaccination. While clinical guidelines have been established to guide vaccination pre-splenectomy and post-BMT, there are limited data to guide timing of COVID-19 or other booster vaccines in adults commencing new or intensified moderate to severe immunosuppression. The comparison of immunity-boosting regimens for COVID-19 upon initiation of immunosuppressive therapy (CIRCUIT) study was designed to address this knowledge gap. CIRCUIT investigates whether administration of a third (or subsequent) COVID-19 booster vaccine ≤2 weeks prior to immunosuppression provides greater anti-spike IgG-mediated immunity than a booster given 24 weeks after new or intensified immunosuppression, that is, week 24 timepoint (Group 1; n=280). Additionally, the research will investigate whether giving a fourth post-BMT COVID-19 booster vaccine at 9 months post-transplant provides greater anti-spike IgG-mediated immunity than a booster given 15 months post-transplant (Group 2; n=40).

**Methods and analysis:**

The CIRCUIT study is an open-label, multicentre randomised clinical trial. Participants will be randomised 1:1 to receive either an additional COVID-19 booster ≤2 weeks pre-immunosuppression and a diphtheria/tetanus toxoids (DT) booster at 24 weeks following new or intensified immunosuppression (week 24 timepoint) or receive a DT booster ≤2 weeks pre-immunosuppression and an additional COVID-19 booster at week 24 (Group 1). Group 2 participants who underwent autologous or allogenic BMT in the last 9 months will be randomised 1:1 to either receive a fourth post-BMT COVID-19 booster at 9 or 15 months post-transplant. The primary outcome will be the integrated time-weighted area under the curve anti-SARS-CoV-2 neutralising antibody (NAb) response over 12 months from a SARS-CoV-2 booster as assessed by a high-throughput SARS-CoV-2 NAb platform assay. Key secondary outcomes of the CIRCUIT randomised control trial will include safety and generation of SARS-CoV-2 antigen specific T and B cell responses.

**Ethics and dissemination:**

The research protocol was approved by the Western Sydney Local Health District Human Research Ethics Committee on 25 August 2022 (Ref no. 2022/PID00782 – 20022/ETH0069). Study results will be published in peer-reviewed medical journals and presented at local and international conferences. All findings regardless of the outcome will be reported.

**Trial registration number:**

NCT05415267.

STRENGTHS AND LIMITATIONS OF THIS STUDYFor the first time, a randomised clinical trial will be used to measure differences in seroconversion to a COVID-19 booster given at baseline versus at 24 weeks in adults commencing new or intensified moderate to severe immunosuppression.This study includes a variety of immunosuppressed adults including those with a haematological malignancy and a range of autoimmune/inflammatory diseases encompassing high burden diseases such as inflammatory bowel disease and multiple sclerosis as well as rarer conditions, sub-stratified by treatment type.The study has statistical power to analyse Group 1 participants as a whole or by distinct substrata-based type of immunosuppression.For pragmatic reasons not all types of conditions associated with immunosuppression are included in the study; exceptions include those with solid organ malignancy, renal transplant recipients, HIV-infected individuals and those with primary immunodeficiencies.In Australia, COVID-19 vaccines can only be administered in state-government mandated centres not by hospital study staff therefore blinding of participants and research staff as to which vaccine was given was not possible and is a limitation of the study.

## Introduction

### Background and rationale

 It was recognised early in the COVID-19 pandemic that immunocompromised individuals were at increased risk of severe disease,^1 2^ delayed viral clearance^3 4^ and death^5 6^ compared with the general population. Immunocompromised individuals comprise heterogenous groups including, but not limited to, those with solid organ and haematological malignancies, those with autoimmune and inflammatory disease on immunosuppressive therapies, allogenic and autologous bone marrow transplantation (BMT) recipients and solid organ transplant recipients. While these groups were prioritised in many COVID-19 vaccine programmes, evidence soon followed that vaccine seroconversion, including titres of anti-SARS-CoV-2 spike protein IgG were lower in immunocompromised individuals compared with healthy comparators. Patients with follicular lymphoma treated with immunochemotherapy had lower anti-spike IgG following two doses of BNT162b2 vaccine compared with those who were untreated and to healthy controls.^7^ Similarly, in patients with Waldenström Macroglobulinemia, those receiving Bruton’s tyrosine kinase inhibitors (BTKis) had lower anti-spike IgG following two doses of BNT162b2 vaccine compared with untreated counterparts and healthy controls.^7^ Studies of a third dose of COVID-19 vaccine in patients with haematological malignancies have demonstrated heterogeneous improvement in anti-spike IgG levels dependent on disease state and therapy. A retrospective observational study of 381 patients with haematological malignancies who received a third dose of a mRNA COVID-19 vaccine found detectable anti-spike IgG in 73.1% of patients after two vaccine doses which rose to 86.4% after three doses.^8^ Rates of seroconversion were lower in patients with chronic lymphocytic leukaemia (CLL) (52.6%) and B cell lymphoma (60.9%).^8^ While the third vaccine dose improved seroconversion for patients on Janus kinase inhibitors (JAKi) (from 57.1% to 90.9%), the rates of seroconversion remained low for patients with haematological malignancies on anti-CD20 treatment (55%), the bcl-2 inhibitor venetoclax (50%) and BTKis (37.5%).^8^ An additional study of 172 patients with CLL/small lymphocytic lymphoma (SLL) who did not seroconvert after two doses of a BNT162b2 vaccine received a third dose of the same vaccine.^9^ Overall, 23.8% of patients with CLL/SLL seroconverted following the third BNT162b2 vaccine with the highest rates among patients who were treatment naïve (40.6%) or off treatment (40%) while lower seroconversion was observed among those on active treatment (12%).^9^ Only one of 28 patients who had received an anti-CD20 B-cell depletion agent in the preceding year seroconverted (3.6%).^9^

B-cell depletion therapies and sphingosine-1-phosphate receptor 1 inhibitors that inhibit lymphocyte egress from lymph nodes have consistently demonstrated detrimental effects on COVID-19 vaccine seroconversion including in the setting of multiple sclerosis^10^ and immune mediated inflammatory diseases.^11^ In patients with inflammatory bowel disease, those treated with tumour necrosis factor-alpha (TNFα) inhibitors had reduced seroconversion to the first two doses of a COVID-19 vaccine compared with those treated with the gut-specific alpha 4 beta 7 (α4β7)-integrin inhibitor vedolizumab.^12^ Autoimmune and inflammatory conditions include both rare and more common diseases and are challenging to study due to the clinical heterogeneity of the underlying conditions and the use of non-protocolised treatment regimens that include both conventional synthetic immunosuppressive agents as well as more targeted immunomodulator therapies. A study conducted in patients with immune-mediated inflammatory diseases receiving their first two doses of BNT162b2 vaccine found median anti-spike IgG levels were lower than in healthy controls at 28 days. Lower median seroconversion responses were also observed in patients receiving both conventional synthetic disease-modifying agents (eg, hydroxychloroquine, methotrexate and sulfasalazine) and targeted biologic therapies eg, anti-interleukin (IL)-6, IL-17, IL-23, TNFα and JAKi.^13^ However, post COVID-19 vaccination serologic responses have not been stratified according to the type of immunosuppression. There is some evidence that patients with autoimmune disease on methotrexate-containing regimens have lower seroconversion responses following COVID-19 vaccinations compared with those not taking methotrexate-containing regimens.^14^ A prospective, open-label randomised control trial which studied 804 immunosuppressed patients, including those with autoimmune/inflammatory disorders, found a suboptimal response following two doses of a COVID-19 vaccine.^15^ 90% of patients categorised as ‘low-responders’ after two doses increased their anti-spike IgG antibodies to the median of the general population, however, 54% of patients categorised as ‘non-responders’ again had no detectable seroconversion after the third dose, suggesting that in some patients a suboptimal serological response cannot always be overcome by administering additional doses.^15^ Again, patients receiving rituximab and other B-cell depletion agents had anti-spike IgG levels markedly below the median of the general population.^15^ Patients treated with corticosteroids and calcineurin inhibitors had mildly reduced seroconversion while those treated with antimetabolites, conventional disease-modifying agents and biologics were less affected.

There are limited data to guide timing of booster vaccine administration around the commencement of moderate-to-severe immunosuppression. Current protocolised clinical guidelines for vaccination in the setting of immunodeficiency predominantly relate to two specific scenarios, those of splenectomy and BMT.

In planned or non-emergency splenectomy, vaccination is recommended at least 2 weeks prior to surgery to prevent overwhelming post-splenectomy infection particularly related to encapsulated bacteria.^16^ The pre-splenectomy schedule includes vaccination to Pneumococcus, meningococcal ACWY, meningococcal B, Haemophilus influenza type B (Hib) with booster doses to Pneumococcus, meningococcal ACWY and meningococcal B given at 2 months and 5 years in addition to a seasonal influenza vaccine.

Vaccination guidelines for adults who have undergone autologous or allogenic BMT advise a comprehensive re-vaccination programme commencing 6 months post-BMT.^16^ Revaccination is required for diphtheria/tetanus (DT; three doses total), Hib (three doses, 4 weeks apart), hepatitis B (three doses at 6, 8 and 12 months post-BMT), pneumococcus (three doses of a conjugate vaccine 4 weeks apart followed by two doses of a 23-valent vaccine), inactivated poliovirus (three doses, 4 weeks apart), MenACWY (two doses, 8 weeks apart), meningococcal B (two doses) and herpes zoster (two doses, 2–6 months apart) with an annual seasonal influenza vaccine also recommended. Additional vaccines given at 24 months post-BMT at the discretion of the treating physician include measles mumps and rubella (two doses, 4 weeks apart) and varicella zoster (two doses, 4 weeks apart) provided there is no evidence of graft-versus-host-disease, and immunosuppressive therapy has been ceased for more than 3 months.

Prior to the COVID-19 pandemic there were limited evidence-based national or international guidelines around the timing of adult booster vaccinations for those with moderate to severe immunosuppression apart from splenectomy and BMT. In response to the COVID-19 pandemic, guidelines advising COVID-19 vaccinations including booster vaccines should be given at least 2 weeks prior to rituximab therapy emerged based on evidence of improved anti-spike IgG seroconversion in patients who had received COVID-19 vaccines 2–4 weeks prior to B-cell depletion.^17^,^19^ However, data relating to other forms of immunosuppression are lacking, and for this reason, the CIRCUIT study was conceived to determine the optimal timing of COVID-19 booster vaccines in two adult patient groups; Group 1: adults commencing new or intensified moderate-to-severe immunosuppression for the treatment of a haematological malignancy or an autoimmune/inflammatory disease and Group 2: adults who have undergone allogenic or autologous BMT in the previous 9 months. Due to a related study running concurrently in Australia,^20^ people with HIV infection and solid organ transplant recipients were not included in the CIRCUIT study.

### Explanation for choice of comparator

Group 1 participants will be randomised to receive either a baseline (week 0) COVID-19 booster prior to commencing new or intensified immunosuppressive therapy and a DT booster at week 24 (Arm A) or a baseline DT booster and a week 24 COVID-19 booster (Arm B).

Participants in Group 2 will have undergone a BMT in the previous 9 months and received three post-BMT COVID-19 vaccines. These participants will be randomised to either receive their fourth post-BMT COVID-19 vaccine at baseline (week 0) (Arm C) or at week 24 (Arm D).

Due to the evolving nature of COVID-19 vaccine development, the study will accept any COVID-19 vaccine licensed for use in Australia. Due to established guidelines on post-BMT vaccination including diphtheria and tetanus, only COVID-19 boosters will be studied in Group 2.^16^

The DT vaccine was selected as the comparator for the COVID-19 vaccine. The DT vaccine is protein-based and stimulates an immune response via a different mechanism to that of currently available mRNA-based COVID-19 vaccines. The study will assess whether the findings that relate to the optimal timing of the COVID-19 booster also apply to more traditional protein-based vaccines. If this is found to be the case, then the study results may have broader implications for vaccinology and optimal clinical guidelines.

### Objectives

This study aims to evaluate the optimal timing of a COVID-19 booster vaccination in adults commencing moderate-to-severe immunosuppression for either an autoimmune/inflammatory disease or a haematological malignancy or who have undergone a bone marrow transplant in the previous 9 months. Efficacy will be assessed primarily by measuring the anti-SARS-CoV-2 neutralising antibody (NAb) response to the booster over 12 months. Other correlates of protective immunity as well as safety and quality of life will be assessed.

Delaying administration of the COVID-19 booster in the deferred arms may lead to higher numbers of breakthrough COVID-19 infections in these arms. The Data Safety Management Board (DSMB) will closely monitor on-study infections and advise the principal investigator and Protocol Steering Committee (PSC) should there be any concerns.

## Methods and analysis

### Patient and public involvement

The study was developed with the support of key consumer organisations including Arthritis Australia, Crohn’s and Colitis Australia, The Leukaemia Foundation and MS Australia. A Leukaemia Foundation representative is a named co-investigator, contributing to the design and execution of the study and is a member of the PSC. Additionally, the study design was presented to The Kirby Institute UNSW’s COVID-19 Community Advisory Board which includes representatives from The Lung Foundation, Spleen Australia and the Transplantation Society of Australia and New Zealand. Following the completion of the study, key results and findings will be disseminated through these and other community stakeholder organisations.

### Trial design

CIRCUIT is an open-label, multicentre randomised clinical trial. Participants with a haematological malignancy or autoimmune/inflammatory disease will be randomised in a 1:1 ratio to receive either an additional COVID-19 booster pre-immunosuppression with a DT booster after 6 months of therapy or a DT booster pre-immunosuppression and an additional COVID-19 booster at 6 months. Participants at least 9 months post-BMT will be randomised in a 1:1 ratio to either receive a COVID-19 booster either following randomisation or after 6 months.

### Trial setting

Eligible participants will be recruited from five academic hospitals throughout Sydney, Australia.

### Eligibility criteria

Systemic autoimmunity and haemato-oncology group (Group 1)

#### Inclusion criteria

Adult aged ≥18 years with a medical condition included in table 1.Previously vaccinated with at least two doses of any licensed COVID-19 vaccine who requires initiation of moderate to severe immunosuppression; the most recent vaccination must have been given more than 3 months prior.Planned significant immunosuppressive therapy for at least 1 year (table 1).No cyclophosphamide, alemtuzumab or rituximab treatment in the past 5 years (concurrent corticosteroids with treatments listed in table 1 are permitted).Voluntary written informed consent.

**Table 1 T1:** Study populations

Group 1*	
**Haemato-oncology**	**Systemic autoimmunity**
Haematological malignancy (excluding bone marrow transplant recipients)† (n=40) B-CLL Follicular or marginal zone lymphoma Multiple myeloma Diffuse large B-cell lymphoma Other haemato-oncology condition at the discretion of the study PI or their delegate	ANCA-positive vasculitis,‡ ANCA-negative vasculitis,‡ Polyarteritis nodosa,‡ Churg-Strauss,‡ Ankylosing spondylitis,‡ Autoimmune hepatitis,§ IgG4 disease,‡ Inflammatory bowel disease,¶** Psoriatic arthritis,‡ Psoriasis, Rheumatoid arthritis,‡ SLE,‡ Sjogren’s syndrome,‡ Myasthenia gravis,†† Multiple sclerosis,‡‡ Autoimmune encephalitis, Neuromyelitis optica,¶ Bullous pemphigoid,¶ Pemphigus vulgaris¶ and variants, Sarcoidosis, Uveitis, other autoimmune/inflammatory conditions diagnosed by a specialist physician and at the discretion of the study PI or their delegate.
	B-cell depletion therapies, eg, rituximab, ocrelizumab, ofatumumab (n=40)
	Anti-metabolite therapies: azathioprine, calcineurin inhibitors, mycophenolate or methotrexate (moderate immunosuppression) (n=40)
	TNFα inhibition (with or without azathioprine or methotrexate or leflunomide to prevent anti-drug antibodies) (n=40)
	Cyclophosphamide or alemtuzumab (severe immunosuppression) (n=40)
	Janus kinase (JAK) inhibitors±leflunomide (n=40)
	Anti-IL-17 and/or 23 monoclonals, eg, secukinumab (n=40)

Group 2
*Bone marrow transplant (n=40)* Haematological malignancy—autologous or allogenic transplant (excluding for treatment of a primary immunodeficiency)

* Eligible patients with both a haematological malignancy and a systemic autoimmune condition are to be enrolled in the haematological malignancy sub-stratum.

† WHO criteria.

‡ EULAR criteria.

§ Biopsy proven.

¶ Mayo criteria.

** Crohn’s Disease activity index.

†† McDonnel I criteria.

‡‡ Must have AChR or Musk autoantibody positive.

AChR, Acetylcholine Receptor; ANCA, Antineutrophil Cytoplasmic Antibodies; EULAR, European Alliance of Associations for Rheumatology; IL, Interleukin; PI, Principal Investigator; TNF, tumour necrosis factor.

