#### Exclusion criteria

Pregnant or breastfeeding.Underlying primary immunodeficiency.Received or likely to receive intravenous/subcutaneous immunoglobulin (IVIg/SCIg).Projected treatment is likely to involve plasma exchange.Contraindication to receipt of a COVID-19 vaccine.Intolerance of or previous allergic reaction to tetanus vaccination.If switching immunosuppressive therapies following enrolment absolute neutrophil count must be above 0.5×10^9^/L at screening.

Bone marrow transplant group (Group 2)

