#### Inclusion criteria

Adult aged ≥18 years with a medical condition included in table 1.Undergone a BMT for a haematological malignancy in the previous 9 months.Previously received at least three post-BMT doses of any licensed COVID-19 vaccine as per current standard of care post-transplant guidelines.^16^Voluntary written informed consent.

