### Sample size

The maximum sample size is 320 participants, 280 in the systemic autoimmunity and haemato-oncology group and 40 in the BMT recipient group. This sample size is based on previously calculated integrated time-weighted AUC of live anti-SARS-CoV-2 NAb titres following two SARS-CoV-2 vaccinations in healthy adults^25^ and patients infected with COVID-19.^26 27^ SD calculated from these datasets were 0.11 log_10_ and 0.12 log_10_, respectively. Assuming an SD of 0.12 log_10_, the study will have over 90% power to detect a 0.13 log_10_ difference in time weighted AUC log_10_ change from baseline (2-alpha=5%) within each sub-stratum of 40 participants. This corresponds to a 35% difference in live virus neutralisation titre between randomised arms. Time-weighted AUC allows for varying of follow-up of participants due to missed visits, loss to follow-up or death. We conservatively estimate overall lost to follow-up to be 10% and mortality 1% balanced across randomised sub-strata.

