### Data collection methods

Following enrolment, research coordinators will collect relevant demographics (age, gender, ethnicity) and clinical data (vital signs, physical measurements, study-qualifying disease diagnosis and treatment plan, medical history, pregnancy status, concomitant medication and COVID-19 infections and vaccinations) on a trial-specific eCRF. Following randomisation and initial booster vaccination, the visit schedule will include eight visits for participants in Group 1 and seven for those in Group 2.

The schedule of study assessments is outlined in online supplemental table 1. Blood samples will be collected at baseline and all on-site follow-up visits for assessment of immunological outcomes. At all study visits, a research coordinator will collect relevant clinical data on the visit eCRF and will review concomitant medication, AEs and SAEs that may have occurred since the last visit. Quality of life assessments at baseline and at weeks 24 and 48 will be self-reported using the validated EQ-5D-3L tool^28^ and participant responses will be entered into the eCRF by the coordinator.

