### Statistical methods

#### Statistical methods for analysing primary and secondary outcomes

Baseline participant characteristics will be summarised by randomised arm for each sub-stratum separately and combined. Primary analyses will compare immunogenicity endpoints between randomised arms on an intention-to-treat basis, that is comparing participants as randomised regardless of whether they received immediate or deferred vaccinations according to the protocol. Log_10_ NAb titres will be summarised at each time point and presented graphically within each stratum. The primary outcome will be time-weighted AUC change from baseline in anti-SARS-CoV-2 log_10_ NAb titre over 12 months. The primary analysis will follow a modified intention to treat approach (mITT) and include all randomised participants with a baseline visit and at least one post baseline time point measured. This approach allows for the inclusion of all participants, even with partial follow-up. The AUC will be calculated for each participant using the trapezoidal rule based on all available data. To assess for bias due to missing data, a secondary analysis which will only include patients who completed the study and have no missing data will be performed. These results will be compared with the mITT analysis. Additionally, if the proportion of patients with missing data is over-represented in one study arm, additional sensitivity analyses will be performed. Randomised arms will be compared within each treatment stratum separately using simple, unadjusted two-sample t-tests. In the event of unbalanced baseline characteristics, adjusted comparisons using linear regression methods may be performed. Results will be presented as mean differences, 95% CIs and p values. There will be no adjustment of p values and CIs for multiple comparisons across the seven sub-strata. In addition to analyses within strata, analyses combining all strata will be performed. Analyses will test for different effects of immediate versus deferred vaccination in separate strata by testing for interactions between strata and randomised arm. These results will be presented as forest plots, by strata and overall. Analysis for Group 2 participants will be presented independently using similar approaches as above as appropriate.

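### Recent SARS-CoV-2 infection enters neither the entry criteria nor the primary model, so a temporarily raised baseline adds variance to an unadjusted change score in comparisons of 20 versus 20

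*Protocol article*

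**What the plan says.** **Entry.** The Group 1 inclusion criteria require that "the most recent vaccination must have been given more than 3 months prior". They give no reason for this interval. Nothing in the inclusion or exclusion lists of either group refers to past SARS-CoV-2 infection; the only COVID-specific exclusion is "Contraindication to receipt of a COVID-19 vaccine". Group 2 needs "Previously received at least three post-BMT doses of any licensed COVID-19 vaccine", with no interval since the last dose or since infection.

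**Data.** Under Data collection methods, the enrolment form captures "COVID-19 infections and vaccinations". Pre-entry infection is therefore known, as far as it was detected. Randomisation in Group 1 is blocked and stratified by treatment sub-stratum only.

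**Endpoint and test.** The Statistical methods section states: "The primary outcome will be time-weighted AUC change from baseline in anti-SARS-CoV-2 log_10_ NAb titre over 12 months". It continues: "Randomised arms will be compared within each treatment stratum separately using simple, unadjusted two-sample t-tests". Linear regression is mentioned only as something that may be done if baseline characteristics turn out unbalanced.

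**Planned precision.** The Sample size section states: "Assuming an SD of 0.12 log_10_, the study will have over 90% power to detect a 0.13 log_10_ difference", within each sub-stratum of 40. The SD comes from healthy adults after two vaccinations and from patients with COVID-19: "SD calculated from these datasets were 0.11 log_10_ and 0.12 log_10_, respectively".

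**The concern.** A change score subtracts the baseline from every later value. A participant infected a few weeks before week 0 starts at a temporary high, and the natural fall from it then counts as a negative response over the following 12 months, whichever arm they are in. With a planned SD of only 0.12 log10, a few such participants in a sub-stratum can widen the spread noticeably.

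Recent infection at entry is foreseeable. The protocol describes implementation during the pandemic phase and expects breakthrough infections on study. It also bars additional boosters because they would alter assessment of the response, so it accepts that another antigen exposure affects this endpoint.

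At stake is the precision of the eight 20-versus-20 comparisons (seven Group 1 sub-strata and Group 2). The planned SD comes from one vaccinated cohort and one infected cohort. Neither is a mix of recently infected and uninfected people receiving a booster, so the SD does not evidently allow for this source of spread.

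**Working it through.** **Inputs from the protocol:** SD 0.12 log10, difference 0.13 log10, two-sided 5%, 20 per arm.

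**Assumed inputs (not in the documents):** the share *p* of entrants with recent infection, and the shift *s* that infection produces in their time-weighted change. Week 0 is taken as the common baseline for both arms.

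**1. The plan's own figure.** Noncentrality = 0.13 / (0.12 × √(2/20)) = 3.43. With 38 degrees of freedom the noncentral t gives power 0.916; the normal approximation gives 0.929. Also 10^0.13 = 1.349, the stated 35%. The claim of over 90% reproduces.

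**2. Size of a shift.** Suppose infection raises baseline by 0.5 log10 and the excess falls linearly to zero by week 24. The change averages -0.25 over weeks 0 to 24 and is -0.5 over weeks 24 to 48:

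s = [(-0.25 × 24) + (-0.5 × 24)] / 48 = -0.375 log10.

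Shifts of -0.25 and -0.10 serve as milder cases.

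**3. Effect on SD and power.** SD = √(0.12² + p(1 - p)s²). For p = 0.10 and s = -0.375: √(0.0144 + 0.09 × 0.1406) = 0.164.

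| Shift (log10) | p = 5% | p = 10% | p = 20% |
|---|---|---|---|
| -0.10 | SD 0.122, power 0.907 | 0.124, 0.899 | 0.126, 0.886 |
| -0.25 | 0.132, 0.860 | 0.141, 0.808 | 0.156, 0.727 |
| -0.375 | 0.145, 0.788 | 0.164, 0.683 | 0.192, 0.550 |

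**4. Spreading the infections out.** The last row treats every infected entrant as being at full peak at week 0. Keep the 0.5 peak and the 24-week decay, but spread infections evenly over the prior 12 weeks. For an infection *u* weeks before entry, the baseline excess is h = 0.5(1 - u/24) and the shift is -h[1 - (24 - u)/96], running from -0.375 at u = 0 to -0.219 at u = 12. Power at 5%, 10% and 20% is then about 0.83, 0.76 and 0.65.

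**5. Chance imbalance.** With p = 10% and independent arms of 20, the arms differ by two or more recently infected participants with probability 0.42, and by three or more with probability 0.18. An excess of two with s = -0.375 moves the arm difference by 2 × 0.375 / 20 = 0.0375 log10.

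**6. Combined Group 1 analysis.** At the worst SD in the table (0.192) with 140 per arm, noncentrality = 0.13 / (0.192 × √(2/140)) = 5.66 and power exceeds 99.9%.

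**7. Cost of two covariates.** With SD 0.12 and 36 instead of 38 degrees of freedom, power is 0.915 against 0.916.

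**The case against.** **Randomisation balances recent infection.** This stands. Allocation is 1:1 and blocked within sub-strata, so no systematic imbalance is expected. What remains is variance and chance imbalance.

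**The size is assumed.** This also stands. Prevalence, peak and decay are not in the documents. Step 4 shows a smaller loss when infections are spread out, and a shift of 0.10 log10 in 10% of entrants costs only about 2 points of power.

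**Stronger readings that a reader might infer:**

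- *That the timing contrast is biased*, because recently infected entrants in the immediate arm are boosted close to infection and those in the deferred arm about six months later. This concerns only an unknown fraction of participants. For them it is a difference in effect within the population the trial chose to enrol, not an imbalance between arms. The documents do not support calling the overall comparison biased.
- *That the vaccination interval exists to avoid a peak baseline, so omitting infection contradicts the protocol's own rule.* No reason for the interval is stated, and it could be a minimum gap between doses. This is a design gap, not an inconsistency.
- *That the entry criteria must change.* Group 1 receives its first booster at most 2 weeks before immunosuppression, so a recently infected candidate could generally not wait 3 months and would be lost. Seven sub-strata of 40 have to be filled at five hospitals. The rule would also miss undiagnosed infection.

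**Covariates belong in the statistical analysis plan.** This holds only in part. The protocol does not leave the matter open: it names an unadjusted test and makes adjustment conditional on observed imbalance. A plan drafted to match would carry that choice forward.

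**Conclusion.** The point holds as a loss of precision that the protocol could avoid. No entry criterion and no planned analysis accounts for recent infection, and the stated primary test ignores a prognostic variable that is already collected. Over the assumed range (5% to 20% of entrants, shift -0.10 to -0.375 log10), sub-stratum power for 0.13 log10 falls from 91.6% to between about 91% and 55%. The lower end rests on every infected entrant being at full peak at week 0 and is pessimistic. The combined Group 1 comparison keeps power above 99.9% throughout. The documents do not show where in this range the trial lies. The case for acting rests on the remedy costing almost nothing, not on a demonstrated large loss.

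**What to change.** In the Statistical methods section, replace the unadjusted two-sample t-test for the primary comparison with a prespecified linear model. Its terms are randomised arm, baseline log10 neutralising titre, and confirmed SARS-CoV-2 infection in the 3 months before baseline. Both covariates are fixed in advance and do not depend on observed imbalance. Baseline titre also picks up part of the effect of undiagnosed infection. Add a sensitivity analysis excluding recently infected participants. Apply both in Group 1 and Group 2.

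State what happens where a sub-stratum contains no recently infected participant: the infection term drops out and baseline titre stays. At p = 5% this has probability 0.95^40 = 0.13 in a sub-stratum of 40.

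The cost is one or two degrees of freedom per sub-stratum (power 0.915 against 0.916 at the planned SD) and a change of analysis wording. It needs no new data collection and can be fixed before data lock, when the analysis plan is due for approval. Eligibility stays as it is.
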